## Abstract

**Introduction:**

Suicide is a global health concern. Sociocultural factors have an impact on self-harm and suicide rates. In Pakistan, both self-harm and suicide are considered as criminal offence’s and are condemned on both religious and social grounds. The proposed intervention ‘Youth Culturally Adapted Manual Assisted Problem Solving Training (YCMAP)’ is based on principles of problem-solving and cognitive–behavioural therapy. YCMAP is a brief, culturally relevant, scalable intervention that can be implemented in routine clinical practice if found to be effective.

**Method and analysis:**

A multicentre rater blind randomised controlled trial to evaluate the clinical and cost-effectiveness of YCMAP including a sample of 652 participants, aged 12–18 years, presenting to general physicians/clinicians, emergency room after self harm or self referrals. We will test the effectiveness of 8–10 individual sessions of YCMAP delivered over 3 months compared with treatment as usual. Primary outcome measure is repetition of self-harm at 12 months. The seconday outcomes include reduction in suicidal ideation, hopelessness and distress and improvement in health related quality of life. Assessments will be completed at baseline, 3, 6, 9 and 12 months postrandomisation. The nested qualitative component will explore perceptions about management of self-harm and suicide prevention among adolescents and investigate participants’ experiences with YCMAP. The study will be guided by the theory of change approach to ensure that the whole trial is centred around needs of the end beneficiaries as key stakeholders in the process.

**Ethics and dissemination:**

Ethics approval has been obtained from the Ethics Committee of University of Manchester, the National Bioethics Committee in Pakistan. The findings of this study will be disseminated through community workshops, social media, conference presentations and peer-reviewed journals.

**Trial registration number:**

NCT04131179.

Strengths and limitations of this studyThis is the first multicentre randomised controlled trial to evaluate clinical and cost-effectiveness of a culturally relevant psychological intervention for young people presenting with self-harm in a low-income and middle-income country.Process evaluation will include in-depth interviews to understand the lived experiences of participants.Stigma, fear of persecution by authorities, peer pressure and educational commitments may act as a barriers to young people participating in the study.The theory of change approach will help mitigate some of the risks around stigma and refusal to participate by involving parents and young people from the inception of the trial.

## Introduction

Suicide is one of the major public health concerns globally with 700 000 suicides each year across the globe.^1^ More than 77% of suicides occur in low-income and middle-income countries (LMICs). However, there are now major concerns about increasing rates of self-harm and suicide among young people in high-income countries such as USA^2^ and Europe.^3^ Overall, suicide is the second-leading cause of death in individuals between 15 and 29 years old.^1^ A recent review reported suicide rates in South Asia to be higher than the global average.^4^ However, such figures are likely to be an underestimate due to a lack of accurate data on suicide in Pakistan^5^ and in many other LMICs.^6^

In Pakistan, a conservative Islamic state, policies are changing but suicide and self-harm (defined below) remain criminal acts and are condemned both socially and religiously as a moral wrong. Suicide and self-harm are often considered taboo subjects across the country, thus contributing to a lack of evidence and under-reporting.^4^ There is, however, accumulating evidence that both self-harm and suicide rates have been increasing in Pakistan but there continues to be notable gaps in evidence.^4^ In a systematic review of mental health studies of adolescents in India, it was found that self-harm is particularly problematic in young people, with 3 months prevalence ranging from 3.9% to 25.4% in community-based studies.^7 8^ Self-harm is one of the strongest predictors of death by suicide.^9^ Self-harm also carries a substantial economic impact and has been associated with large treatment costs in Pakistan.^10^ Adolescents with a history of self-harm are at a higher risk of repeating this later in life,^11^ thus there is an important need to develop effective interventions in order to avoid long-term burden.

In adolescents, self-harm is the result of a highly complex interplay between genetic, biological, psychological, social and cultural factors.^11^ Common set of risk factors and psycho-social mechanisms for self-harm within LMICs include being female, experiencing interpersonal conflict, suffering from abuse (including domestic/family/gender based violence), hopelessness and being diagnosed with psychiatric disorder.^4^ Other psychological influences include feelings of entrapment, a lack of belonging or connection.^12^ Research in Pakistan is imperative to explore the effectiveness of interventions for potential risk factors to reduce rates of self-harm and suicide.^13^ The WHO Report ‘preventing Suicide: A Global imperative’ recommends ‘twofold’ public health approach for suicide prevention, that is, to identify the issues, and provide treatment for high-risk individuals.Considering the benefits of adult individual cognitive–behaviour therapy (CBT)-based psychotherapy,^14^ tested in our previous trial in Pakistan with positive results^15^ and replicated in our recently completed trial with 901 adults participants in which we had to exclude 265 adolescents (less than 18 years) (Culturally adapted Manual Assisted brief Psychological intervention, CMAP2).^16^

An unmet need was recognised to develop CMAP further for adolescent and adapting the similar brief psychological intervention for children and adolescents. Psychological therapies that work in western culture cannot always be implemented in a different culture and adaptation is considered to be essential^17 18^

Since interpersonal conflicts with family members are a commonly reported precipitant of self-harm episodes in Pakistan.^4 13^ It has been reported that problem-solving therapy ‘CMAP‘ may be a useful intervention for prevention of self-harm in Pakistan.^13^ This psychological intervention, using variants of CBT that are age appropriate for the local culture and customs in Pakistan, may prove to be beneficial in reducing self-harm in adolescents.^15^ Before this intervention can be implemented at a larger scale, there is a need for establishing its clinical and cost-effectiveness via the proposed trial. We cannot assume that an intervention developed for adults would be suitable for children and adolescents and since self-harm remains a major problem in young people, this planned trial fills an important gap and clinical need.

## Methods and analysis

### Objectives

This study includes both quantitative and qualitative aspects.

The objectives of the quantitative component are:

To determine the clinical effectiveness of Youth Culturally Adapted Manual Assisted Problem Solving Training (YCMAP) over 12 months based on the following outcomes:Primary outcome:To measure the effectiveness of YCMAP in comparison to treatment as usual (TAU) in terms of repetition of self-harm 12-month postrandomisation. This will be assessed using adapted Suicide Attempt Self-Injury Interview (SASII).^19^Secondary outcomes:Suicidal ideation will be assessed using the ‘Beck Scale for Suicidal ideation’.^20^Feelings of hopelessness will be assessed using the ‘Beck Hopelessness Scale’.^21^Level of distress will be assessed using a 10-item scale the ‘Kessler Psychological Distress Scale’.^22^EQ-5D- Y will be used to assess ‘health-related quality of life’.^23^Client Satisfaction Questionnaire-8 will be used to assess participants’ satisfaction with services.^24^Translated versions of all these scales have been developed and used in previous trials CMAP1 (15) and CMAP 2 (13) by following established protocols for translating such measures.^25^ The scales which were not available in Urdu were translated for an MPhil project (Brief psychological intervention for adolescents who self harm, IPP/BU/ER/103/1377) and reviewed in initial Patient and Public Involvement and Engagement (PPIE) meetings.Assessments will be carried out at baseline, completion of the intervention (3 months), 6, 9 and 12 months after randomisation. See figure 1 belowTo determine the cost-effectiveness of the YCMAP intervention over 12 months.

**Figure 1 F1:**
[figure not shown]
Flow diagram of the YCMAP study. TAU, treatment as usual; YCMAP, Youth Culturally Adapted Manual Assisted Problem Solving Training.

The objectives of the qualitative component are:

To explore the experience of participants with YCMAP and their perception about benefits and negative or adverse consequence of it.To explore in detail participants’ reasons for continuing (completer) or not continuing (drop out) with the study.To explore clinicians and other stakeholder views (such as school teachers) on the YCMAP and its impact.To explore therapists’ perspective on the delivery of the YCMAP.

The expected outputs of the study are:

A manual-assisted evidence based intervention—the YCMAP, ready for integration into the healthcare services.Standardised training and supervision package—a resource pack and training programme on ‘how to do it’ for use across health services.Information tool-kit for the families and the wider community. This will be service-user defined and will be used to increase awareness about mental health in general and self-harm and suicide in young people in particular.

### Inclusion criteria

Adolescents meeting the study inclusion criteria will be invited to take part in the study by their primary care clinician, ward or emergency room clinician who is making the initial assessment. In the context of this study, self-harm is defined as: ‘an act with non-fatal outcome, in which an individual deliberately initiates a non-habitual behaviour that, without interventions from others, will cause self-harm, or deliberately ingests a substance in excess of the prescribed or generally recognised therapeutic dosage, and which is aimed at realising changes which the subject desired via the actual or expected physical consequences’.^26^

Age: 12–18 years.History of recent self-harm which is defined as ‘self-harm occurring within the last 3 months (from the initial identification of a potential participant)’. This period is considered as high risk for repetition in young people.^11^Resident in the trial catchment area.All participants known to clinical or health services. This will be necessary to ensure all participants have access to TAU.

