### Sample size

The sample size is based on the primary outcome, repetition of self-harm in a 12-month period (yes/no). The TAU arm of the study has an expected self-harm rate of 20%.^7^ A clinically important effect would be a reduction to 7.5% in the intervention group. Under these presumptions, and assuming a 5% significance level and 90% power, a study with no clustering would require 158 patients per arm. The study has a partially nested design due to therapist clustering in the YCMAP arm. Our sample size calculation has taken account of this by adjusting the sample size upwards, conservatively assuming clustering in both arms. Based on previous analysis of therapist trials, we believe that the intraclass correlation coefficient (ICC) is likely to have a value between 0.01 and 0.05 for this type of outcome measure. Assuming an ICC of 0.05, and a cluster size of 16 patients per therapist, a design effect of 1.75 is calculated. This increases the numbers required to 277 per arm. Furthermore, based on our previous work there is expected to be a 15% loss to follow-up, and so the final numbers recruited will be 326 per arm, with a total sample of 652 participants.

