### Statistical analysis

Statistical analysis will be based on intention-to-treat principles, subject to the availability of data. During the course of the trial, periodic random quality checks of data will be carried out by the trial statistician blind to treatment allocation. Once data entry has been completed, preliminary data analysis will be carried out blind to treatment allocation, prior to unblinding. The results of the trial will follow the standard Consolidated Standards of Reporting Trials recommendations. Baseline and follow-up data will be summarised using the appropriate descriptive statistics and graphical summaries. Treatment effects will be presented with 95% CIs. We will investigate baseline factors that predict nonresponse using a logistic random effects model as non-response may be clustered by therapy group. The statistical analysis of the primary outcome measure (repetition of the self-harm episode within 12 months) will be based on a logistic random effects model with randomised treatment, age, gender and type of self-harm as fixed effects and a random effect of therapist in the treatment arm, with individuals in the control arm being treated as clusters of size 1. The continuous secondary outcome measures will calculate treatment effects using a linear mixed model, with a random effect of therapist and the set of baseline covariates as above including baseline values of the outcome where available. A single model will be fitted across all time points, with a fixed effect for time, and interactions between time and treatment group. There will be no adjustment to secondary outcomes CIs for multiple testing. Binary secondary outcomes will take a similar approach to continuous outcomes, but will use logistic random effects models.

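### The study-wide definition of self-harm requires a non-fatal act, so a suicide with no earlier recorded repeat does not count in the primary outcome

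*Protocol article*

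**What the plan says.** The definition stands in the protocol article under Inclusion criteria. It is introduced with "In the context of this study, self-harm is defined as" and starts "an act with non-fatal outcome, in which an individual deliberately initiates a non-habitual behaviour". A second limb covers overdose: "or deliberately ingests a substance in excess of the prescribed or generally recognised therapeutic dosage". The Introduction already points forward to this definition and names suicide as something separate: "suicide and self-harm (defined below) remain criminal acts".

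The primary outcome uses the same term throughout. Objectives compares the arms "in terms of repetition of self-harm 12-month postrandomisation", assessed with an adapted Suicide Attempt Self-Injury Interview (SASII). Sample size treats the outcome as yes or no over 12 months. Statistical analysis describes it as "repetition of the self-harm episode within 12 months", fitted with a logistic random effects model, by intention to treat as far as data are available.

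No section gives the outcome its own definition, adds suicide to it, or relaxes either restriction for follow-up.

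**The concern.** The non-fatal restriction suits entry, because only survivors can enrol. It does not suit the endpoint of a trial that aims to prevent repetition in young people at raised risk of suicide. The Introduction itself calls self-harm one of the strongest predictors of death by suicide, so a suicide during follow-up is foreseeable.

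If such a death is scored as no repetition, it counts as a success for the arm in which it happened. If it is treated as missing, it drops out of the comparison. Either way the arm's risk is understated, and an imbalance in suicides between arms would bias the treatment effect in favour of the arm with more deaths.

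The word non-habitual raises a smaller question of the same kind: whether a genuine recurrence could be discounted because it continues an established pattern.

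**Working it through.** **1. Does the definition reach the outcome?** The introductory words make it study-wide, the Introduction refers to it from outside the eligibility section, and the primary outcome is stated as repetition of the defined term with no alternative. On the text, the outcome inherits the definition.

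**2. What happens to a suicide?** The definition requires a non-fatal outcome, so the act is not an event. The only stated instrument is an interview, which the participant can no longer give. A suicide preceded by a recorded non-fatal repeat still scores yes. A suicide with no earlier recorded repeat becomes either a no or a missing value; the article does not say which.

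**3. The plan's own figures** (Sample size: 20% versus 7.5%, 5% significance, 90% power, ICC 0.05, 16 patients per therapist, 15% loss).
- Two-sided comparison of two proportions, pooled variance, no continuity correction: 158 per arm.
- Design effect: 1 + (16 − 1) × 0.05 = 1.75; 158 × 1.75 = 276.5, rounded up to 277.
- Loss to follow-up: 277 / 0.85 = 325.9, rounded up to 326; 2 × 326 = 652.

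All stated figures reproduce. The arithmetic is not at issue.

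**4. Size per uncounted death, with 277 analysed per arm.**
- Planned difference: 20 − 7.5 = 12.5 points. Expected events: 0.20 × 277 = 55.4 (TAU) and 0.075 × 277 = 20.8 (YCMAP).
- Scored as a non-event: 1/277 = 0.36 points.
- Treated as missing: in YCMAP, (20.8 + 1)/277 − 20.8/276 = 0.33 points; in TAU, (55.4 + 1)/277 − 55.4/276 = 0.29 points.
- The article gives no suicide rate. For an assumed 2 to 4 such deaths in one arm and none in the other, scored as non-events: 2/277 = 0.7 to 4/277 = 1.4 points.
- Equal numbers in both arms, scored as non-events, leave the risk difference unchanged. Only an imbalance shifts it.

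**5. What does non-habitual exclude?**
- It qualifies the behaviour limb only. Repeat overdose falls under the second limb and counts.
- Self-harm that becomes habitual after randomisation must first recur. That earlier repeat already scores yes on a binary 12-month outcome, and nothing later reverses it.
- What remains is a participant who enters through a qualifying episode, has an older habit of self-harm, and whose only repeats continue that habit. The documents give no frequency for this.

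**The case against.** The definition sits under Inclusion criteria. The adapted SASII may have its own counting rules, and a full protocol or analysis plan, not shown, may deal with deaths. An article is not expected to carry those details. A non-fatal repetition endpoint with deaths reported separately is also a recognised choice. Suicides may be few, and with assessments at 3, 6 and 9 months some participants who die would already have a recorded repeat.

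Much of this stands as a limit on size. It does not remove the point, which is not that a detail is absent: the article states a study-wide rule excluding fatal acts and then uses the defined term as its primary outcome. If a fuller document counts suicide, the published wording conflicts with it. The article does not state that it chose a non-fatal endpoint with deaths handled separately.

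Two stronger readings are tempting, and the documents support neither.
- A reader might infer that suicides are explicitly scored as no repetition. The article does not say so; non-event and missing are the two results its wording leaves open.
- A reader might infer that many habitual repeaters are lost, with a material loss of power. If an assumed 10% of repeaters were dropped in both arms, power would fall from 0.90 to 0.86, and at an assumed 30% to 0.75. Nothing in the documents supports any such fraction, and the group affected is only the narrow one identified above.

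**Conclusion.** The concern holds for suicide. By the written definition, a suicide without an earlier recorded repeat does not count against the arm where it occurs. This is a question of the endpoint's validity, not of power or sample size. Each such death moves an arm's risk by about 0.36 points if scored as a non-event, or about 0.3 points if missing, assuming 277 analysed per arm and the planned event rates. The total effect is unknown because no suicide rate is given; at the small assumed counts above it is modest against 12.5 points.

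The non-habitual wording is a secondary ambiguity, confined to participants whose only repeats continue a habit from before entry. Both conclusions rest on the published article. They would change if an unseen document defines the outcome differently, but the article's wording would then need to be brought into line.

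**What to change.** Keep the existing definition for eligibility. State the primary outcome separately: any repeat self-harm recorded on the adapted SASII, or death by suicide known to the trial, within 12 months of randomisation. Add that a repeat is not discounted because it is habitual. Report non-fatal repetition alone as a sensitivity analysis.

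The design, recruitment target and model stay as they are. There are two costs.
- The endpoint becomes slightly broader. If suicides without an earlier repeat added an assumed 0.5 or 1 percentage point to both arms, power at 277 analysed per arm would move from 0.90 to 0.89 or 0.88.
- Cause of death must be classified, preferably by someone unaware of allocation, from whatever follow-up contact and safety reporting provide. The article does not describe how deaths are ascertained. Its Introduction reports stigma and under-reporting, and it plans for 15% loss to follow-up, so some suicides may stay unknown. The plan should say how a death of uncertain cause is handled.

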### Exclusion criteria

Patients with a severe mental illness such as schizophrenia spectrum and other psychotic disorders, bipolar and severe depressive disorder will be excluded. This intervention has been developed to help individuals who experience common mental health problems such as anxiety or mild to moderate depressive disorders. It has not been developed to work with people with severe mental health difficulties such as psychotic disorders. We consider that the intervention would require work with service users and carers and further adaptation work with people who have severe mental health illness.Patients with conditions limiting engagement with assessment/intervention.Temporary resident unlikely to be available for follow-up.

### Design

A multicentre rater blind randomised controlled trial (RCT) with randomisation by individual participants in order to compare the YCMAP in addition to TAU with TAU alone.

### Study site and population

Study sites are all participating primary care clinics, emergency departments and medical wards of general hospitals in five major cities of Pakistan, Karachi, Hyderabad, Lahore, Multan and Rawalpindi.

### Sample size

The sample size is based on the primary outcome, repetition of self-harm in a 12-month period (yes/no). The TAU arm of the study has an expected self-harm rate of 20%.^7^ A clinically important effect would be a reduction to 7.5% in the intervention group. Under these presumptions, and assuming a 5% significance level and 90% power, a study with no clustering would require 158 patients per arm. The study has a partially nested design due to therapist clustering in the YCMAP arm. Our sample size calculation has taken account of this by adjusting the sample size upwards, conservatively assuming clustering in both arms. Based on previous analysis of therapist trials, we believe that the intraclass correlation coefficient (ICC) is likely to have a value between 0.01 and 0.05 for this type of outcome measure. Assuming an ICC of 0.05, and a cluster size of 16 patients per therapist, a design effect of 1.75 is calculated. This increases the numbers required to 277 per arm. Furthermore, based on our previous work there is expected to be a 15% loss to follow-up, and so the final numbers recruited will be 326 per arm, with a total sample of 652 participants.

